## Abstract

**Background:**

Pharmaceutical care is the direct interaction between pharmacist and patient, in order to improve therapeutic compliance, promote adequate pharmacotherapeutic follow-up, and improve quality of life. Pharmaceutical care may be effective in reducing complications and in improving the quality of life of patients with chronic diseases, like Chagas heart disease, while bringing a positive impact on health system costs. The morbidity and mortality indexes for patients with Chagas heart disease are high, especially if this heart disease is complicated by heart failure. In this setting, we hypothesize that pharmaceutical care might be an important tool for the clinical management of these patients by improving their quality of life, as a better compliance to their treatment and the avoidance and prompt correction of drug-related problems will minimize their symptoms, improve their functional class, and decrease the number of hospital admissions. Therefore, the aim of this trial is to evaluate the contribution of pharmaceutical care to clinical treatment of patients with Chagas heart disease complicated by heart failure.

**Methods/design:**

A prospective, single-center randomized clinical trial will be conducted in patients with Chagas heart disease complicated by heart failure. A total of 88 patients will be randomly assigned into two parallel groups: an intervention group will receive standard care and pharmaceutical care, and a control group will receive only standard care. Both groups will be subjected to a follow-up period of 12 months. The primary outcome of this trial is the evaluation of quality of life, measured by the 36-item short-form and the Minnesota Living with Heart Failure Questionnaire. Secondary outcomes include drug-related problems, exercise tolerance as measured by the standard six-minute-walk test, and compliance.

**Discussion:**

Patients with Chagas heart disease complicated by heart failure under pharmaceutical care are expected to improve their quality of life, present with a lower incidence of drug-related problems, improve their functional capacity, and improve in their compliance to treatment.

**Trial registration:**

ClinicalTrials.gov Identifier: NCT01566617

## Background

Chagas disease is still a major public health problem in Latin America. About 10 million people worldwide are estimated to be infected with *Trypanosoma cruzi*, mostly in Latin America and 20 to 30% of these individuals are expected to present cardiac complications during their lifetime [1]. According to the Brazilian Ministry of Health, there are still about 2.5 million individuals living with chronic Chagas disease in Brazil and, in 2009, 4,700 deaths attributed primarily to Chagas disease were reported in Brazil [2].

Chagas disease has two distinct clinical phases, acute and chronic [3]. The majority of acute cases are clinically silent and last for 6 to 8 weeks. Only less than 10% of acute cases will present a self-limiting febrile illness, which can be aggravated by acute myocarditis. The acute phase is followed by a chronic phase, which has three forms: indeterminate, cardiac, and digestive. The indeterminate chronic form is a long-lasting asymptomatic phase, when patients present reactive serologic tests for Chagas disease but there is no evidence of damage to any organ [3-5]. However, two or more decades after infection, 20 to 30% of the patients will progress to the cardiac form of the disease, when the majority of the deaths and severe complications related to the disease occur [6-8]. Patients at the chronic cardiac phase may manifest heart failure (HF), ventricular and atrial arrhythmias, atrioventricular blocks, thromboembolism, stroke, and sudden death [8-10], with a high economic and mortality burden. Another 10 to 15% of the patients at the chronic phase will present evidence of digestive disease characterized by complaints of dysphagia or constipation and radiologic evidence of megaesophagus or megacolon [11]. An unspecified number of patients may present evidence of a mixed chronic form with evidence of both cardiac and digestive involvement [9].

Heart failure is a clinical syndrome that arises secondary to changes of cardiac structure or function that impair the ability of the left ventricle to fill or eject blood. The clinical manifestations are dyspnea, fatigue, and edema with impairment of functional capacity and quality of life of affected individuals. Heart failure is currently classified by the American Heart Association into four stages: A (patients at risk of developing HF); B (patients who have structural heart disease known to be associated with HF); C (patients with symptomatic HF); and D (patients with HF refractory to treatment) [12].

The treatment of patients with chronic Chagas heart disease is aimed at controlling symptoms and improving patients’ quality of life, by preventing cardiovascular complications, limiting disease progression, and increasing the overall survival rate of the patients. Unfortunately, there is no specific treatment against the parasite that can benefit patients at this stage, and treatment follows the guidelines issued to treat HF and arrhythmias due to complications caused by other etiologies [12].

In the proposed trial, we will focus on the contribution of pharmaceutical care to clinical treatment of patients with Chagas heart disease complicated by HF. The pharmacological treatment of patients with chronic Chagas heart disease complicated by HF includes such drugs as angiotensin-converting enzyme (ACE) inhibitors [13] or angiotensin II receptor blockers, beta blockers [14-18], aldosterone antagonists [18,19], digitalis, and loop diuretics. Many of these pharmacological strategies can prolong the life expectancy of patients with HF and are recommended in patients with Chagas heart disease complicated by HF [9]. Other drugs may be required as specific HF complications, such as atrial fibrillation, occur. For example, atrial fibrillation and ventricular arrhythmias will require drugs such as antiarrhythmics [12,18,20].

Another important aspect of HF treatment is the control of precipitating factors. Precipitating factors are any factors that can trigger an episode of decompensated HF. These include poor dietary or medical compliance, inappropriate discontinuation or reduction of HF therapy by the physician, use of medications known to worsen HF, inadequately treated hypertension, anemia, arrhythmias, and acute myocardial ischemia. Poor medical compliance and use of medications known to worsen HF, such as nonsteroidal anti-inflammatory drugs, calcium antagonists, thiazolidinediones, class I antiarrhythmic agents, and sotalol, are potentially preventable precipitating factors that can be minimized by pharmaceutical care [12,21]. Pharmaceutical care is a practice performed by the clinical pharmacist who delivers the patient’s prescription, in order to improve compliance, avoid underuse of appropriate drugs and optimize their dosage, avoid use of inappropriate drugs, and detect, prevent, and resolve drug-related problems (DRPs) [22] and improve the patient’s quality of life [24]. The value of this strategy has been demonstrated in distinct clinical scenarios [23-25]. In patients with HF, this intervention may improve patients’ symptoms, avoid hospitalizations, and, consequently, improve patients’ quality of life. In fact, small, short-term trials and observational data suggest that pharmaceutical care intervention reduces the risk of hospital admission and possibly mortality in patients with HF [26,27].

Drug-related problems are health problems linked to drug therapy that may affect expected results of patients’ therapy and their quality of life, while causing a high economic and mortality burden [28]. In the United States alone, the annual related costs of DRPs have been estimated as 177.4 billion dollars [29]. Several factors may contribute to DRPs, such as access to drug therapy, noncompliance to drug therapy, prescription duplicity, ineffectiveness of drug therapy, adverse drug reactions (ADRs), and dosage above the therapeutic range [30].

Chronic diseases, such as HF, impose a great limitation on the patients’ quality of life [31] and the success of treatment strategies for HF is measured not only by the increase in event-free time survival but also by the improvement in the quality of life of the patient [21]. Pharmaceutical care may improve a patient’s quality of life related to HF [21] and it is important to test this hypothesis in patients with Chagas heart disease complicated by HF, who, in Brazil, are mostly assisted in public outpatient services. Therefore, our aim is to evaluate the effect of pharmaceutical care, as compared with standard care, on the quality of life of patients with Chagas heart disease complicated by HF.

## Methods/design

### Study design

The proposed clinical trial will be held at a single center, the Evandro Chagas Clinical Research Institute (IPEC), which is one of the technical scientific units of the Oswaldo Cruz Foundation (Fiocruz). IPEC is a 93-year-old institution fully dedicated to clinical research in infectious diseases, including Chagas disease, among others. IPEC is a major reference center for research, care, and training on Chagas disease.

This is a double-blinded, controlled, superiority (parallel) clinical trial with balanced randomization [1:1] that will be conducted for adult volunteers with Chagas disease complicated by HF. The patients’ functional status will be classified according the New York Heart Association (NYHA) functional classification system from I to IV. All patients at our institution are treated following current guidelines for diagnosis and management of HF in adults [12].

The cardiologists from our outpatient center will refer patients with chronic Chagas disease complicated by HF to the pharmacist. The pharmacist will explain the study in detail and obtain the patients’ informed consent. All included patients will undergo a screening phase, which includes a review of the patient’s medical records and an interview for assessment of eligibility. All eligible patients will complete quality-of-life questionnaires and take a six-minute-walk test after inclusion. After the screening phase, patients will be randomly assigned to one of two groups: an intervention group, who will receive standard care plus pharmaceutical care, and a control group, who will receive only standard care.

Each patient will be followed for 12 months. All patients from both groups will take part in medical consultations every month. After each medical consultation, a pharmacist blinded to the patient’s assignment will interview all patients, to identify compliance to treatment and any DRPs. After this, all patients will interact with the clinical pharmacist. Those randomized to the control group will receive all prescription medications, while those patients randomized to the intervention group will not only receive all prescription medications but will also undergo pharmaceutical care, to solve DRPs, confirm, and reinforce their compliance to the medical prescription. Whenever the pharmacist identifies a DRP in the intervention group, he will interact with the physician, to solve the DRP. All patients will take part in a pharmaceutical consultation at the end of the follow-up, to identify DRPs, complete quality-of-life questionnaires, and perform six-minute-walk tests. The pharmacists who will deliver the initial evaluation before randomization, the monthly evaluations of DRPs and compliance, and the final evaluation at the end of the follow-up period will be blinded to the patients’ assignment (Figure 1).

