### Interventions: pharmaceutical care vs. standard care

The pharmaceutical care applied in this trial will be based on Dáder methodology. The Dáder method for pharmaceutical care is a systematic process developed by the Research Group of Pharmaceutical Care at the University of Granada, Spain [32]. This method includes patient education about cardiovascular drugs, patient counseling about lifestyle modifications, assessment of drug compliance, identification of underuse of appropriate drugs, optimization of drug dosage, and identification of the use of inappropriate drugs, to enable the pharmacist to deliver treatment recommendations to physicians and contribute to relieving DRPs [32] and improved quality of life [21,23].

Those patients randomized to standard care will receive all prescription medications from the pharmacist and basic instruction on how to use them.

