#### Protection against risk

The informed consent process will be conducted according to good clinical practices. The potential study patients will sign an informed consent form after reading it, receiving adequate explanations, and understanding the study objectives and procedures. Illiterate patients may bring in relatives or friends to read for them, testify, and sign the consent form: if this is not possible, we can enroll a patient, and a witness will sign the consent form. The formal informed consent process will be accomplished and documented before any other study-related procedures. Adequate time will be allowed for the patient to ask questions. All aspects of the study will be explained to the patients, including, but not limited to, potential risks and benefits, and the amount of time required from the patient, including the number of study visits expected. All patients will be informed that participation is voluntary, that refusal to participate will involve no penalty or loss of benefits to which the patient is otherwise entitled, and that the patient may discontinue participation at any time without penalty or loss of benefits to which the patient is otherwise entitled.

The investigators will see patients at regular intervals. Patients who miss a scheduled study visit will be contacted by telephone to schedule a new visit. Case report forms will identify patients only by the study number. All records identifying patients by name and information linking patients’ names with study ID numbers will be kept in locked rooms in locked cabinets and will be accessible only to study personnel. We will provide patients with the names and telephone numbers of the principal investigator and sub-investigators, and they will be advised that they are allowed to make reverse-charge telephone calls. Information regarding the patient’s medical history will be obtained with the patient’s consent. Regarding this proposal, the procedures are considered to offer minimal risks for the patients. The patients may derive direct benefits derived from research and the knowledge acquired may potentially improve the health care of other patients suffering from Chagas disease. Therefore, the benefits of this research will fall into two major categories: benefits to patients and benefits to society. Patients will not receive any kind of remuneration, but will be reimbursed for travel expenses and meals.

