### Blinding

The pharmacists who will carry out the initial evaluation before randomization, monthly evaluations of DRPs, and compliance, and the final evaluation of the health care questionnaires after the end of the patient follow-up will be blinded to the patient’s assigned group. Physicians conducting the six-minute-walk test will also be blinded to group assignment.

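### The trial is labelled double-blinded, but only the outcome evaluators are blinded, so the self-reported primary endpoint and compliance are not protected from reporting bias

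*Protocol article*

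**What the plan says.** Under Study design, the protocol article states: "This is a double-blinded, controlled, superiority (parallel) clinical trial with balanced randomization".

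The Blinding section lists who is blinded. First come "The pharmacists who will carry out the initial evaluation before randomization, monthly evaluations of DRPs, and compliance, and the final evaluation" of the questionnaires at the end of follow-up. Then: "Physicians conducting the six-minute-walk test will also be blinded to group assignment". The account of monthly visits under Study design also blinds the evaluating pharmacists. Nobody else is named.

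On delivery, Study design says that "those patients randomized to the intervention group will not only receive all prescription medications but will also undergo pharmaceutical care". For the comparator, the Interventions section says: "Those patients randomized to standard care will receive all prescription medications from the pharmacist and basic instruction on how to use them". On contact with doctors, Study design says: "Whenever the pharmacist identifies a DRP in the intervention group, he will interact with the physician, to solve the DRP". On consent, the section on protection against risk says: "All aspects of the study will be explained to the patients".

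The Outcomes section makes quality of life the primary endpoint, measured by SF-36 and MLHFQ. Compliance, a secondary endpoint, is self-reported on the four-question Morisky scale.

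**The concern.** Readers usually take double-blind to mean that the patients, and commonly those treating them, do not know the assignment. Here the label sits beside a design in which only evaluators are blinded and the two arms receive visibly different services.

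This matters most where the patient supplies the data. For SF-36, MLHFQ and Morisky the respondent is in effect the assessor. A patient who knows that he or she is receiving the extra service may score quality of life or adherence more favourably for that reason alone. Compliance is especially exposed, because the service itself reinforces compliance and patients are then asked whether they comply.

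If the label carries into the results report, a difference in these outcomes will be read as free of reporting bias, although the design cannot exclude it. The Discussion section intends the results to be the basis for larger studies.

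**Working it through.** **Step 1: who is blinded, according to the article.**

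| Party | Stated as blinded? | What the design implies |
|---|---|---|
| Pharmacists doing baseline, monthly and final evaluations | Yes (Study design; Blinding) | Blinded |
| Physicians running the walk test | Yes (Blinding) | Blinded |
| Clinical pharmacist delivering care | No | Must know the arm to give or withhold the service |
| Patients | No | Told about the study at consent, then receive either the full service or dispensing with basic instruction; no sham described |
| Treating physicians | No | Learn the arm for intervention patients in whom a DRP is raised |

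Awareness among patients is an inference, not a statement in the text. It is close to unavoidable given full explanation at consent and an overt service.

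**Step 2: what evaluator blinding protects.**

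| Outcome | Source of the data | Effect of evaluator blinding |
|---|---|---|
| SF-36, MLHFQ (primary) | Patient's answers | Does not remove reporting bias |
| Morisky compliance | Patient's answers | Does not remove reporting bias |
| DRPs | Identified and classified by a blinded pharmacist | Real, though incomplete, protection |
| Six-minute walk | Distance, measured under a blinded physician | Real, though incomplete, protection |

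**Step 3: illustration of scale.** No figure in the article follows from the blinding label, so there is no stated figure to reproduce or correct. The calculation below shows only how sensitive the test would be to a reporting shift.

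Inputs from Sample size calculation: SD 10.9, 40 per group, target difference 10.3 points. Assumed, because the documents give no value: a reporting shift b of 2, 3 or 4 points on a true effect of zero. Statistical methods rejects at P < 0.05 without giving sidedness, while Sample size calculation plans at one-sided 1%, so both levels are shown (taking the 0.05 as two-sided).

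- Standard error of the difference: 10.9 × √(2/40) = 2.437.
- Noncentrality: b / 2.437.
- Rejection probability: from the noncentral t distribution with 40 + 40 − 2 = 78 degrees of freedom, critical value 1.991 (two-sided 0.05) or 2.375 (one-sided 0.01).

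| Assumed shift b | Share of 10.3 | Noncentrality | Rejection, two-sided 0.05 | Rejection, one-sided 0.01 |
|---|---|---|---|---|
| 2 | 19% | 0.821 | 12.8% | 6.4% |
| 3 | 29% | 1.231 | 22.9% | 13.2% |
| 4 | 39% | 1.641 | 36.7% | 23.8% |

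Without any shift the values would be 5% and 1%.

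**The case against.** The strongest reply is that the article already tells a careful reader the truth. The Blinding section lists exactly who is blinded and never claims that patients are, and the abstract does not use the double-blind label. That is correct, but it confirms that the label under Study design is wrong.

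A second reply is that contact is largely matched. Both arms have monthly medical consultations, a monthly interview with a blinded pharmacist and then contact with the clinical pharmacist, and controls receive basic instruction. This stands: the contrast is not between monthly counselling and nothing, and the matching reduces the difference in attention. It does not hide which service the patient receives.

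A third reply is that the question is pharmaceutical care against standard care, and education and counselling are part of that care. A genuine response to the pharmacist's attention is therefore partly the effect under test, not bias. This also stands. Answers coloured by knowing the assignment remain a separate matter, and the design cannot tell the two apart.

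Three stronger readings are tempting and are not supported:

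- A reader might infer that the trial has no protection from bias at all. Evaluator blinding protects DRP identification and the walk test, and the sealed-envelope procedure under Randomization and concealment protects against selection.
- A reader might infer that the walk test is unblinded, because Outcomes lets a cardiologist instruct the patient. The text does not say that this is the treating cardiologist, and the Blinding section requires walk-test physicians to be blinded. A breach would be a failure to follow the plan, not an error in it.
- A reader might infer that physicians know the assignment of every patient. The text supports this directly only for intervention patients in whom a DRP is raised.

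**Conclusion.** The point holds in limited form. Double-blinded is a stated property that the described design does not have. The trial is assessor-blinded with openly delivered care, and the primary endpoint and compliance are self-reported by patients who will in practice know their arm. An open design is legitimate for this kind of service; the fault lies in the label and in the conclusion that it invites.

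The size of any reporting bias cannot be derived from the documents. The figures of about 13-37% at two-sided 0.05 and about 6-24% at one-sided 0.01 rest wholly on assumed shifts of 2 to 4 points and on a true effect of zero. They show sensitivity and are not an estimate of bias in this trial. The conclusion about the label does not depend on them.

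**What to change.** Under Study design, replace the double-blinded label with: *assessor-blinded; patients, the pharmacist delivering care and treating physicians not blinded*. Add a sentence stating that the estimated quality-of-life and compliance differences include any effect of patients' awareness of assignment, and carry the same limit into the conclusions.

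This changes wording only. Sample size, analysis and conduct stay as they are. The cost is a slightly less favourable design claim.

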**Figure 1 F1:**
[figure not shown]
**General overview of study protocol.** 6MWT, six-minute-walk test; DRPs, drug-related problems; HF, heart failure.

